## Abstract

**Introduction:**

Co-occurring psychiatric conditions and concerning behaviours are prevalent in individuals with autism spectrum disorders (ASD), and are likely to be detrimental to functioning and long-term outcomes. The cognitive rigidity and deficits in emotional literacy and verbal behaviour that commonly occur in ASD can adversely affect clinicians’ confidence to identify concerning behaviours and mental health problems. There is a need to develop a measure that is tailored towards individuals with ASD, and differentiates between symptoms of psychopathology and core ASD symptoms. Furthermore, it should be modified to capture internalising symptoms that individuals with ASD may find difficult or be unable to verbalise. This protocol describes the intended development and validation of the Assessment of Concerning Behaviour (ACB) scale. The ACB will aim to be a multidimensional measure of concerning behaviours in ASD incorporating self-report, parent/carer, teacher/employer and clinician report versions that can be used across the lifespan and spectrum of intellectual ability.

**Methods and analysis:**

This study will be guided by the methods described in the US Food and Drug Administration Guidance for Industry Patient-reported Outcome Measures. A literature review, cognitive interviews and focus groups with individuals who have experience of working or living with ASDs will be used for item generation. A sample of children and adults with ASD will complete the ACB, in addition to other gold standard measures of concerning behaviour in order to establish the initial psychometric properties of the scale.

**Ethics and dissemination:**

This study has received ethical approval from the NHS Research Ethics Committee: London-Camden and King's Cross (ref: 15/LO/0085). Study findings will be disseminated to healthcare professionals and scientists in the field through publication in peer-reviewed journals and conference presentations.

Strengths and limitations of this study
A strength of this study is that it will follow US Food and Drug Administration guidelines for the development of patient-reported outcome measures. Consequently, it will seek extensive input from service users, parents, families and those with experience of working with autism spectrum disorders.All participants will be asked to complete the study questionnaires twice allowing for an assessment of questionnaire sensitivity to change in this initial psychometric evaluation of the instrument.A potential limitation of this study is that study questionnaires will be completed in participants’ homes. One may be uncertain about the extent to which measures are completed independently. However, some participants will be completing questionnaires in clinic settings which will allow us to explore levels of support which informants require to complete the questionnaire.

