ACB, Assessment of Concerning Behaviour Scale; ASD, Autism Spectrum Disorders; ICC, Intraclass Correlation Coefficient.

Participants’ questionnaire battery will be presented in HealthTracker™, a web-based platform for online completion (www.healthtracker.co.uk) that is currently being used in two EU FP7 projects—the Suicidality: Treatment Occurring in Paediatrics (STOP study; http://www.stop-study.com) and the Managing the Link and Strengthening Transition from Child to Adult Mental Health Care (MILESTONE) project (http://www.milestone-transitionstudy.eu). HealthTracker™ has also been used in a previous questionnaire development and validation study.^25^ The web-based questionnaires will follow the principles of data protection, security levels for health data, have an audit trail and Good Clinical Practice compliance. Participants will be given a unique ID number and log-in information, and will be asked to complete the questionnaires independently. All participants, including those with literacy issues, will have the option of going through the questionnaires over the phone with a member of the research team. Participants will also be able to complete paper versions of the questionnaires if requested. Questionnaire completion should not take longer than approximately 60 min for adults and 40 min for children.

Participant medical records will be accessed to validate the ACB against details of diagnoses obtained from patient case notes as well as against Development and Well-being Assessment (DAWBA^26^) diagnoses, IQ and treatment/medication status if they are available in case notes. Consent will be obtained to access medical notes. For children recruited via schools, the research team will also request details about IQ, educational attainment and diagnoses from school records. Parental consent will be obtained to do this. Where measures of IQ are not available from participant medical/school records, a brief measure of IQ will be collected by the research team (see table 1).

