###### Inter-rater reliability

Intraclass correlations will be used to assess inter-rater agreement between pairs of scores provided by two different raters (eg, self-report vs parent/carer; parent/carer vs teacher). Coefficients will be calculated at the subscale and total score levels. As this is an exploratory study, weighted Cohen's κ values will also be calculated to assess inter-rater reliability at the item level.

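### Support with completion is to be explored only among clinic completers, so the self–parent ICC may be biased upward by an unknown amount unless help is recorded on every self-report form

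*Protocol article*

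**What the plan says.** The strengths and limitations list in the Abstract of the protocol article states the problem openly: "A potential limitation of this study is that study questionnaires will be completed in participants’ homes", and "One may be uncertain about the extent to which measures are completed independently". It then offers an answer: "some participants will be completing questionnaires in clinic settings which will allow us to explore levels of support". The sentence goes on to say that this means the support informants need in order to complete the questionnaire. Neither the number of clinic completers nor how they come to complete there is given.

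Under Phase 2, Main sample, each participant receives an individual ID and log-in to a web platform said to "have an audit trail and Good Clinical Practice compliance". Participants "will be asked to complete the questionnaires independently". Paper forms are available on request, and all participants, including those with literacy problems, "will have the option of going through the questionnaires over the phone with a member of the research team".

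Under Inter-rater reliability, "Intraclass correlations will be used to assess inter-rater agreement between pairs of scores provided by two different raters". Self-report against parent/carer is the first example and parent/carer against teacher the second.

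The exclusion criteria for Phase 2 remove people who cannot, or are not expected to be able to, complete questionnaires.

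**The concern.** An ICC between self-report and parent report measures agreement only if the two scores were produced separately. If the parent who supplies one half of the pair also helped to answer the other half, part of the agreement is shared authorship, and the error runs towards higher agreement.

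The stated remedy does not reach this problem. Watching how much support people need in clinic tells the team about support needs. It does not identify which home forms were answered with help, or whether the helper was the rating parent.

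What is at stake is the interpretation of the self-report version. In Self-report measures in ASD, the article reads moderate parent–patient correlations as a sign that each source adds something of its own. An upward bias would blur that. The higher coefficient could be taken as evidence that self-report works well, or as evidence that it is redundant, and neither reading would be safe.

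**Working it through.** **No figure to reproduce.** The article gives no sample size or precision for self–parent agreement. The calculation below is a sensitivity check on assumed inputs.

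**Inputs from the article**
- Parent–patient correlations of 0.44, 0.42 and 0.36 for externalising problems, internalising problems and social skills (Self-report measures in ASD). The middle value is used as the starting point; treating it as agreement without assistance is an assumption.
- Main sample of 200, about 100 adults and 100 children (Phase 2 sample size).

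**Inputs that are assumed**
- f, the share of self-reports assisted by the rating parent: 10% to 75%.
- λ, the share of an assisted score that comes from the parent: 0.25 or 0.50.
- Equal means and unit variances, and a consistency-type ICC.

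**Model.** Assisted self score = (1−λ)·self + λ·parent. With r the unassisted correlation:
- variance of an assisted score: Va = (1−λ)² + λ² + 2λ(1−λ)r
- covariance with the parent score: Ca = (1−λ)r + λ
- pooled: V = (1−f) + f·Va and C = (1−f)r + f·Ca
- ICC = 2C/(V+1)

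**Worked case, r = 0.42, λ = 0.25, f = 0.25**
- Va = 0.5625 + 0.0625 + 0.1575 = 0.7825; Ca = 0.315 + 0.25 = 0.565
- V = 0.75 + 0.25 × 0.7825 = 0.9456; C = 0.315 + 0.25 × 0.565 = 0.4563
- ICC = 0.9125/1.9456 = 0.47

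**Results from r = 0.42**

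| Share assisted (f) | ICC, λ = 0.25 | ICC, λ = 0.50 |
|---|---|---|
| 0% | 0.42 | 0.42 |
| 10% | 0.44 | 0.46 |
| 25% | 0.47 | 0.51 |
| 50% | 0.52 | 0.61 |
| 75% | 0.58 | 0.72 |

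For f from 10% to 75%, starting from 0.36 gives a range of 0.38 to 0.68, and starting from 0.44 gives 0.46 to 0.73.

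**A harsher assumption.** If assisted pairs agree at 0.90, the pooled value is a weighted average:
- 10% assisted: 0.9 × 0.42 + 0.1 × 0.90 = 0.47
- 25% assisted: 0.75 × 0.42 + 0.25 × 0.90 = 0.54
- 40% assisted: 0.6 × 0.42 + 0.4 × 0.90 = 0.61

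**Against sampling error.** The Fisher interval is tanh(atanh(0.42) ± 1.96/√(n−3)). The 95% limits are 0.24 to 0.57 at n = 100 and 0.30 to 0.53 at n = 200, if every participant yields a pair. Light assistance (0.44 to 0.47) sits well inside both. Frequent and strong assistance (0.61, 0.72) lies outside both. Unlike sampling error, this bias does not shrink as pairs are added.

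**Is help at home plausible?** The article does not say that it occurs. Children enter from age 7, about half the main sample are children, and the IQ target puts 15% + 40% = 55% below 70. These figures make help plausible; they do not measure it.

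**The case against.** The strongest reply is that the authors declare the limitation themselves and have taken steps against it. They ask for independent completion, issue individual log-ins, offer a phone route with a researcher that bypasses the parent, and exclude people who cannot complete questionnaires. The clinic sentence is about support needs and does not claim to correct the ICC. The article also condenses a fuller protocol, and form-level fields may be specified there. The study describes its item-level agreement work as exploratory, no threshold is attached to the self–parent ICC, and the parent–teacher pair is untouched by this mechanism.

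Much of this stands as mitigation. It does not remove the point, because a request is not a record and a log-in does not show who sat beside the participant. The article says that the platform has an audit trail but not that the trail captures helpers. After all these steps the article still calls independence uncertain, and the one answer it gives cannot classify home forms.

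Several stronger readings are tempting and are not supported:
- That agreement will be inflated. The article nowhere says that parents help with self-reports. Only a possible bias of unknown size follows.
- That the bias is uncorrectable. A restricted analysis of clinic or phone completers is possible, although those groups may be selected and it leaves home forms unclassified. Recording help avoids the difficulty.
- That clinic completion contradicts the web, phone and paper routes. Those are modes and clinic is a place, so there is no conflict.
- That the roughly 75% recruited through clinics sizes the clinic group. That figure is the recruitment source, not the place of completion.
- That the one-week repeat may switch mode. The article is merely silent on this, and it concerns test–retest reliability.

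**Conclusion.** The point holds in a limited form. The article names a threat to independence and answers it with information from a setting where the threat is different. As a result, the self–parent ICC may be biased upward by an unknown amount, and forms completed at home cannot be sorted afterwards into assisted and unassisted unless help is noted at completion.

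Under the assumed model, from a starting value of 0.42, the shift runs from nothing (no parental help), through 0.02 to 0.05 (a quarter of the score from the parent in 10% to 25% of forms), to about 0.30 (half the score in 75% of forms). The share assisted and the strength of influence are assumptions; the article supports no particular value for either.

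A reader might conclude that only unassisted pairs should count. That does not follow, because such pairs would probably come from more able participants, against the article's aim of covering the IQ range in population proportions.

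**What to change.** Add brief unscored closing items to every self-report ACB, in all modes and settings (web, paper, phone, clinic):
- setting and mode of completion;
- whether anyone helped;
- who helped (parent/carer, teacher, researcher, other);
- whether the helper read items aloud, explained them or answered them.

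Add one sentence to Inter-rater reliability: the self–informant ICC will be reported overall, and separately for pairs in which that informant did and did not help, with each stratum described by IQ and age. The stratified values supplement the overall estimate and do not replace it. In the limitations list, cite these items as the answer to uncertain independence, and keep the clinic observation for what it can show, namely support needs. If the full protocol already holds such items, a reference to them is enough.

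The cost is a few tick-boxes per form, smaller strata with wider intervals, and an unassisted stratum likely to be more able. Self-reported help may also be under-declared. The article says that the study is already recruiting, so the items should be in place before Phase 2 forms are completed.

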## Introduction

Autism spectrum disorders (ASD) are characterised by restrictive and repetitive interests and behaviours, impaired social and communication skills,^1^ and have a prevalence rate of approximately 1%.^2^ ASD is associated with poor long-term psychosocial impairment^3^ and substantial burden on the individual, their family and caregivers in addition to social and economic burden.^4^
^5^

Observational studies have revealed high levels of concerning behaviours in ASD that are likely to be of further detriment to long-term functioning and outcomes. Throughout this protocol, the term ‘concerning behaviour’ will be used to refer to any behaviours or emotions that may cause concern for individuals with ASD, their parents/carers or healthcare professionals. Concerning behaviours are likely to have a negative impact on the functioning or well-being of the individual with ASD, their family/carers or wider society. Concerning behaviours could themselves form important treatment targets or could be indicative of the presence of a co-occurring condition requiring further investigation. Among others, concerning behaviours that commonly occur in ASD include aggression, anxiety, phobias, hyperactivity, compulsive behaviour, depression, suicidal ideation or attempted suicide and sleep disorders.^6–11^ While prevalence rates of co-occurring conditions and concerning behaviours in ASD vary among studies, this is likely due to methodological differences in populations assessed (eg, population or clinic-based samples) and measurement instruments used (eg, screening or diagnostic tools). Nonetheless, each of these listed concerns are consistently reported as occurring more frequently in individuals with ASD compared to typically developing populations.^6^

However, many clinicians lack confidence in identifying and evaluating co-occurring conditions in ASD. The presence and heterogeneity of ASD symptoms, intellectual disability and difficulty with communication, can complicate the identification of co-occurring conditions in individuals with ASD who may present with atypical symptoms of psychopathology.^12^ Furthermore, diagnostic overshadowing can lead to symptoms of psychopathology being wrongly attributed as core ASD symptoms^6^ (eg, existing social anxiety may be misinterpreted as lack of social interest).

Early and accurate identification of common concerning behaviours and co-occurring conditions in ASD are paramount, given that symptoms may be more amenable to intervention compared to the core symptoms of ASD.^13–17^ Furthermore, established concerning behaviours and coexisting conditions may be more resistant to treatment;^18^ later diagnosis of co-occurring conditions is related to increased risk of hospitalisation.^19^

### Self-report measures in ASD

Another factor complicating the identification of co-occurring conditions in ASD is the use of self-report measures. In typically developing populations of youth, multi-informant reports incorporating self-report measures are seen as the gold-standard for the assessment of mental well-being. ASD is associated with cognitive rigidity, difficulties with emotion recognition and labelling (alexithymia), and deficits in social cognition; such characteristics are likely to lead to differences in the interpretation of self-report measures that have been validated in typically developing and other clinical populations.

A recent meta-analysis has shown that levels of informant agreement in ASD are similar to levels seen in typically developing populations. Correlations between parent and patient report were moderate (r=0.44, 0.42 and 0.36 for externalising problems, internalising problems, and social skills, respectively;^20^), indicating some agreement, yet unique information being provided by parents and self-reports. It is important that self-report measures are not overlooked when assessing individuals with ASD. However, measures should be modified to the unique needs of individuals with ASD and should be validated in this population.

To the best of our knowledge, no questionnaire currently exists that is targeted towards individuals with ASD, includes self-report versions, and is able to screen for coexisting conditions in ASD individuals. This is possibly because existing measures precede the current understanding that many people with ASD and related developmental disorders also have symptoms and disorders that could benefit from other evidence-based treatment.

### Aim

This protocol outlines the intended development and validation of the ‘Assessment of Concerning Behaviour Scale’ (ACB). The term ‘concerning behaviour‘ was chosen for the title of the questionnaire based on feedback from patient and public involvement panels (PPI panels; including parents of individuals with ASD and individuals with ASD) who disliked the use of the other terms including ‘psychopathology’, ‘abnormal behaviour’, ‘maladaptive behaviour’, ‘symptoms’, ‘challenging behaviour’ and ‘mental health problems’.

The ACB aims to be a multidimensional screening measure of concerning behaviours in ASD. The measure is not intended as a diagnostic tool of co-occurring conditions, but aims to identify the presence of symptoms that may require further, more in-depth assessment. The measure will assess the severity of concerning behaviours to allow for assessment of symptom severity and treatment response over time. It is intended primarily for clinical use, but will also be appropriate for use as an outcome in clinical trials.

The study aims to develop self-report, parent/carer, teacher/employer and clinician report versions that can be used across the lifespan and spectrum of intellectual ability. The aim is to make the resulting questionnaire approximately 40 questions in length that should not take longer than 20 min to complete.

This project is being conducted as part of a larger National Institute for Health Research (NIHR)-funded research project entitled ‘Improving Autism Mental Health’, reference number: RP-PG-1211-20016.

### Methods and analysis

This study will be guided by the methods described in the US Food and Drug Administration (FDA) Guidance for Industry Patient-reported Outcome Measures.^21^ It will involve an iterative process with the following stages: concept identification, concept elicitation, cognitive interviews for instrument refinement and instrument validation. The FDA guideline was chosen as the most appropriate given its emphasis on patient input in order to ensure content validity of the questionnaire. Furthermore, following the FDA guidance will allow the instrument to be used as an outcome measure in clinical trials.

## Phase 1: Qualitative development of the ACB

### Tool review

Initial PPI feedback, collected prior to the start of this project, indicated that a brief, single instrument was needed to capture and assess the multitude of concerning behaviours experienced by individuals with ASD. A brief literature review has been conducted and revealed that no screening tool currently exists that has been developed specifically for use in the ASD population. The research team will draw on extensive clinical experience in the assessment of individuals with ASD, and refer to tools commonly used in clinical practice (eg, the Aberrant Behaviour Checklist, the Developmental Behaviour Checklist) as well as relevant review articles^22^ to identify factors to be considered in the assessment of concerning behaviour in ASD.

### Concept identification

Initially, a literature review will identify concerning behaviours that commonly occur in ASD to be included in the questionnaire. A draft version of the instrument incorporating all these constructs will be created. The draft version will be presented for review to a panel of experts with at least 5 years of clinical experience in ASDs in order to confirm the findings of the literature search, and identify missing constructs. A second draft version will be created based on feedback from the expert panel.

### Concept elicitation

The next stage of the study will involve focus groups with individuals with experience of living or working with ASD. Separate focus groups will be conducted with clinicians and mental health professionals specialising in child and adult ASD and associated conditions, teachers working with children with ASD, parents/carers of children/adults with ASD and children, young people and adults with ASD themselves.

The focus groups will explore which concerning behaviours and feelings affect people with ASD. The groups will follow a semistructured format using open-ended questions to allow participants to discuss their experiences and views. Participants will be asked to discuss behavioural and emotional issues that are additional to the core symptoms of ASD. Focus groups will discuss how these issues present, and how they differ and are distinct from core ASD characteristics. Participants’ views on the initial items developed for the questionnaire (from the literature review and feedback from an expert panel) will also be sought. Participants will be asked about items that they feel are important to be included, as well as items which are irrelevant. Focus groups will be audio recorded, and each group will include approximately 4–8 participants (with the exception of child and adult patient focus groups where a maximum of three patients will be invited in an attempt to avoid overwhelming participants). All participants will be asked to complete a demographic questionnaire during this session.

After completion of the focus groups, a thematic analysis, following the principles of thematic analysis proposed by Braun and Clarke,^23^ will be conducted on the recorded and transcribed data. The concerning behaviours and emotions discussed by participants will be placed into meaningful clusters and groups. Any ‘clusters’ or themes identified in the analysis that were not captured by the literature review and expert panel consultation will be created into items, using language used by participants in the focus groups, where possible.

A third draft of the questionnaire will be created incorporating participants’ feedback. Items generated by the group discussions will be added, while items deemed irrelevant or not important by group members will be deleted. It is expected that approximately 150–200 items will be generated through the literature review and expert feedback, and the focus groups will reduce this number to between 40 and 70 items.

PPI panels recruited for the NIHR grant will also be consulted at this stage, to provide their feedback on this version of the questionnaire.

